## Abstract

**Background:**

Accumulating evidence suggests that the metabolic effects of metformin and fermentable fibers are mediated, in part, through diverging or overlapping effects on the composition and metabolic functions of the gut microbiome. Pre-clinical animal models have established that the addition of fiber to metformin monotherapy improves glucose tolerance. However, possible synergistic effects of combination therapy (metformin plus fiber) have not been investigated in humans. Moreover, the underlying mechanisms of synergy have yet to be elucidated. The aim of this study is to compare in adolescents with obesity the metabolic effects of metformin and fermentable fibers in combination with those of metformin or fiber alone. We will also determine if therapeutic responses correlate with compositional and functional features of the gut microbiome.

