### Statistical methods

#### Statistical methods for primary and secondary outcomes {20a}

Descriptive statistics will summarize all study variables. Prior to analysis, numerical variables with skewed distribution will be transformed (e.g., log_2_ or cubed root) or a comparable nonparametric test will be used. Between-group comparison of primary and secondary outcomes will be performed at baseline and two consecutive time points independently using unpaired *t*-tests (comparing two groups) or analysis of variance (three groups) and chi-square tests for numerical and categorical data, respectively. Impact of the three interventions on IR (HOMA-IR, primary endpoint) over time will be compared using linear mixed models, after adjusting for relevant confounders, including pubertal stage if any statistically significant difference is observed between treatment groups at baseline. OTU relative abundance will be compared between treatment groups. Statistical analyses for gut microbiota community composition will include principal coordinates analysis and canonical correlation. Linear discriminant analysis Effect Size [78] and multivariate association with linear models will be used to identify specific OTUs that differentiate the treatment groups. Mediation modeling will be employed to provide further insights on possible casual pathways to explore whether the gut microbiota may play a causal or mediation role in the physiological effects detected [79]. Treatment responders versus non-responders will also be evaluated. We will characterize the ecological differences prior to the intervention, and then the individualized response to the intervention in order to assess the role of the microbiome in the host’s metabolic response to the intervention. For this analysis, we will apply a machine learning approach called partition around medoids clustering [80]. Separate models will be estimated for secondary endpoints, which are exploratory, but nevertheless important. Intervention types and times will be included as fixed effects in linear mixed models. Pearson or Spearman correlation coefficients will be computed between changes in gut microbiome composition/function and insulin resistance, hormones, metabolites, and inflammatory markers.

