## Discussion

This study will compare the metabolic benefits of fiber with those of metformin in adolescents with obesity, determine if metformin and fiber act synergistically to improve IR, and elucidate whether the metabolic benefits of metformin and fiber associate with changes in fecal microbiota composition and the output of health-relevant metabolites. The study will thereby assess the relationship between therapeutic intervention(s) and putative mechanisms that are hypothesized to underlie the clinical effects. Overall, we predict that the combination of MET and fiber will have a synergistic effect, being more effective than MET or fiber alone at 12 months in improving IR and BMI in the adolescents with obesity. We further predict that these metabolic benefits will be associated with changes in gut microbial composition and metabolic functions (assessed by 16S rRNA gene amplicon sequencing, fecal SCFAs and bile acids, and targeted plasma metabolomics) and measures of systemic inflammation and intestinal barrier function (assessed by plasma cytokine, LBP, and fecal calprotectin). If successful, our proposed combination therapy may help to interrupt the cycle of weight gain and IR, thereby reducing the risk for developing T2DM, a worldwide public health concern, in adolescence and adulthood.

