In summary, this study will determine the efficacy of MET and fermentable fibers alone or in combination on metabolic control, while also determining if the effects are related to individual differences in microbiome composition and functions. Thus, this study will demonstrate whether the gut microbiome represents a promising target for enhancing therapeutic efficacy and for further preventing T2DM in at risk adolescents. The results of this study may be integrated into clinical practice guidelines for the prevention of youth-onset T2DM and also aid in the development of novel microbiota-targeted therapies for adolescents with obesity and associated metabolic comorbidities.

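### The planned microbiome–metabolic correlations name no adjustment for arm, so coefficients taken over all participants can reflect treatment-group differences rather than individual tracking

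*Protocol article*

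**What the plan says.** The last sentence of section {20a} reads "Pearson or Spearman correlation coefficients will be computed between changes in gut microbiome composition/function and insulin resistance, hormones, metabolites, and inflammatory markers". It does not say whether the three arms are pooled, analysed one at a time, or adjusted for.

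Arm appears in the sentence just before, but for another method: "Intervention types and times will be included as fixed effects in linear mixed models". The subgroup section {20b} says that age and sex differences are examined arm by arm. Arm handling is therefore written down elsewhere in the plan, but not for the correlations.

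The aim that the correlations serve is in the abstract's Background: "We will also determine if therapeutic responses correlate with compositional and functional features of the gut microbiome". The Discussion adds a prediction, "We further predict that these metabolic benefits will be associated with changes in gut microbial composition and metabolic functions", and its closing summary promises "determining if the effects are related to individual differences in microbiome composition and functions".

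Section {20a} also plans other work on mechanism. Mediation modelling is to "explore whether the gut microbiota may play a causal or mediation role in the physiological effects detected". A responder comparison with clustering looks at "the individualized response to the intervention in order to assess the role of the microbiome in the host’s metabolic response to the intervention". On secondary endpoints the section says: "Separate models will be estimated for secondary endpoints, which are exploratory, but nevertheless important".

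**The concern.** The question in the Discussion is about individuals: do participants whose microbiome changed more also gain more? A two-variable correlation over a mix of three randomised arms answers a different question. Its value has two parts: covariation between individuals inside an arm, and covariation of the arm means. If the combination arm does better on insulin resistance and also shows a larger microbiome change, as the article predicts, the second part is positive even when the first is zero. A by-product of treatment with no bearing on metabolism could then be reported as associated with benefit.

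The error can also run the other way. If fiber moves the microbiome feature and metformin moves insulin resistance, the arm means pull against each other and can hide a true within-arm link. Either result would feed into the article's conclusion on whether the microbiome is a promising target.

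**Working it through.** The article gives no figure for the correlation analysis, so there is none to reproduce. The check asks how often a pooled coefficient is significant when the within-arm correlation is zero.

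**Inputs from the article.** Allocation is 1:1:1 with 30 per arm (Trial design {8}). Attrition is 15%, so 30 × 0.85 = 25.5, or about 26 per arm and N = 78. The HOMA-IR effect sizes are 0.75 for metformin and 0.86 for PGX (Sample size {14}).

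**Assumptions.** Each change has SD 1 within arm and is coded so that positive means improvement. The microbiome shift is varied from 0.5 to 2.0 SD. The test is two-sided at 5%; the article names no level for the correlations. The values 0.75 and 0.86 are used only as plausible sizes for a between-arm difference.

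**Formula.** Let one of three equal arms differ by *a* SD on the feature and *b* SD on the host measure. The variance of arm means 0, 0, *a* is [2(a/3)² + (2a/3)²]/3 = 2a²/9, and the covariance of the arm means is 2ab/9. With zero within-arm correlation:

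r = (2ab/9) / √[(1 + 2a²/9)(1 + 2b²/9)]

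For a = b = 0.75: 0.125/1.125 = 0.111. For a = b = 0.86: 0.164/1.164 = 0.141. For a = 1.5, b = 0.75: 0.25/√(1.5 × 1.125) = 0.192. The critical |r| is 0.223 at N = 78 and 0.207 at N = 90.

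**Rejection rates** (20,000 simulated trials, Pearson, combination arm shifted only):

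| Shift, feature / host (SD) | Pooled r | 26 per arm | 30 per arm | Arm-adjusted |
|---|---|---|---|---|
| 0.5 / 0.5 | 0.05 | 7% | 8% | 5% |
| 0.75 / 0.75 | 0.11 | 16% | 18% | 5% |
| 0.86 / 0.86 | 0.14 | 24% | 27% | 5% |
| 1.5 / 0.75 | 0.19 | 41% | 45% | 5% |
| 1.5 / 1.5 | 0.33 | 89% | 93% | 5% |
| 2 / 2 | 0.47 | 99.8% | 99.9% | 5% |

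Spearman is within about one percentage point of these.

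**Other patterns, 26 per arm.**
- Both variables shifted in both fiber arms (the same formula holds when two of three arms share a shift): 17% at 0.75/0.75 and 49% at 1.5/0.86.
- Feature shifted 1.5 SD in both fiber arms, HOMA-IR shifted 0.75 SD in the combination arm only: r = 0.125/√(1.5 × 1.125) = 0.096, rejection 13%.
- Both variables shifted equally in all three arms: 5%.
- Uncorrelated arm means, for example feature 0, 1, 1 and insulin resistance 0.5, 0, 1 in MET, FIBER and combination. The covariance is [(−0.667)(0) + (0.333)(−0.5) + (0.333)(0.5)]/3 = 0, rejection 5%.

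**Masking.** Let the true within-arm correlation be 0.35, the feature be moved 1.5 SD by fiber (0, 1.5, 1.5) and HOMA-IR 0.75 SD by metformin (0.75, 0, 0.75). The covariance of arm means is [(−1)(0.25) + (0.5)(−0.5) + (0.5)(0.25)]/3 = −0.125. Their variances are 0.5 and 0.125. The pooled r is (0.35 − 0.125)/√(1.5 × 1.125) = 0.173, below the critical 0.223. Simulated power is about 32% pooled and 88% to 89% adjusted for arm.

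**The case against.** The strongest reply is that pooling is inferred. The sentence never says that the arms are combined, within-arm coefficients would also fit it, and those hold the nominal 5%. The source is a condensed article and the analysis plan is not shown. This stands as a limit on the claim. It does not remove the point, because the article names a two-variable method for these data while it states how arm is handled elsewhere. On the plain reading, the named method does not match the individual-level aim.

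A reader might infer that these correlations will be significant whenever treatment shifts both variables. The documents do not support that. At shifts of 0.75 to 0.86 SD in one arm the rate is 16% to 24%. It is 5% for shifts common to all arms or uncorrelated arm means, and it nears certainty only at about 1.5 to 2 SD on both variables.

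The figures also rest on borrowed inputs. In the article, 0.75 and 0.86 are effects of metformin and PGX on HOMA-IR, not the advantage of the combination over either monotherapy, and no microbiome shift is given. This is conceded: the rates are illustrations over a range.

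A reader might also infer that the individual-response aim rests on these coefficients alone. It does not: mediation modelling and the responder and clustering analysis address it too. They do not correct the coefficients, however, which would be reported in their own right.

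Finally, if the microbiome carries part of the treatment effect, between-arm covariation is signal, and removing it leaves an observational association open to confounding by adherence, diet and activity. That is fair. It argues for keeping the two sources apart and labelled, not for one coefficient that blends them.

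**Conclusion.** The point holds in a limited form. As written, the correlations carry no adjustment for arm. If taken over all participants, they cannot by themselves show that benefit tracks individual microbiome change. With 26 per arm and no individual-level link, the false-positive rate is about 16% to 24% when both variables shift 0.75 to 0.86 SD in the combination arm only, and higher for larger assumed shifts. In the masking example, power falls from about 89% to 32%.

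This rests on three things: pooled computation, arm means that differ in a related pattern (or, for masking, an opposing one), and assumed microbiome shifts. The primary HOMA-IR comparison is not affected. The analysis serves a stated but exploratory mechanistic aim, so the change is worth making but does not bear on the trial's main result.

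**What to change.** Amend the last sentence of section {20a} to say that correlations between changes will be partial correlations (Pearson or rank-based) adjusted for arm, with the three within-arm coefficients shown beside them. Add that an unadjusted coefficient over all participants, if reported, is descriptive and will not be read as evidence that benefit tracks individual microbiome change. If within-arm or adjusted coefficients were always intended, the same sentence settles it.

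Adjusting for baseline values and the sex/age stratum is optional. The mediation and responder/clustering analyses stay as separate evidence.

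No new data are needed. Arm costs two degrees of freedom (from N − 2 = 76 to N − 4 = 74 at N = 78). The within-arm coefficients will be imprecise at about 26 each, and the adjusted coefficients remain exploratory and observational.

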#### Interim analyses {21b}

No interim analyses will be completed.

#### Methods for additional analyses (e.g., subgroup analyses) {20b}

We plan to do a subgroup analysis for age and sex differences within each arm.

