### Objectives {7}

The primary objective is to compare the efficacy of MET (850 mg p.o. twice/day) versus FIBER (35 g/day supplemental fiber) alone versus combined MET plus FIBER on IR (as estimated by homeostatic model assessment of insulin resistance [HOMA-IR]) in adolescents with obesity, IR, and family history of T2DM.

The secondary objective is to compare the effects of the study therapies alone or in combination on:
Changes in the Matsuda, insulinogenic, and oral disposition indices as determined by OGTTChanges in body weight, BMI percentile and *z*-score, and body composition (fat mass, fat-free mass, and fat mass to fat-free mass ratio)Changes in quality of life (QoL) and perceived hunger and satietyChanges in fasting metabolic (glucose, adiponectin, and lipids) and satiety markers (acylated ghrelin, peptide tyrosine tyrosine [PYY], GLP-1, and leptin)Changes is measures of systemic inflammation (C-reactive protein, interleukin 6, and tumor necrosis factor-α [TNF-α]) and intestinal barrier function (lipopolysaccharide-binding protein (LPB) and fecal calprotectin)Changes in gut microbiome composition and functions (fecal microbiota composition, fecal SCFAs and bile acids, and targeted plasma metabolomics [amino acids, branched chain ketoacids, acylcarnitines, ceramides, trimethylamine *N*-oxide, choline, and betaine])

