### Trial design {8}

A single-center, parallel three-armed, double-blinded, 12-month randomized controlled trial with a 1:1:1 allocation ratio. Ninety adolescents (*n* = 30 per arm) with obesity, IR, and family history of T2DM will be enrolled in the trial matched for sex and age (Figs. 1 and 2).

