## Interventions

### Explanation for the choice of comparators {6b}

We postulate that the therapeutic effects of both MET and fermentable fibers are mediated, in part, through diverging effects on the gut microbiome, and that MET plus fiber combination therapy will act synergistically to improve glucose tolerance in adolescents with obesity and IR. By combining MET with fiber, we anticipate that the improvement in IR and BMI will be significantly higher when compared to each monotherapy. A control group without treatment is not included, since a no treatment arm would be unethical for adolescents with obesity and IR.

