## Assignment of interventions: allocation

### Sequence generation {16a}

After having provided written informed consent/assent, participants will undergo a baseline assessment and be randomized to one of the three intervention groups A, B, and C (i.e. MET, FIBER, MET + FIBER) via computer-generated numbers and stratified by age and sex, using the adaptive (dynamic) randomization (Step 2, Fig. 3). Each group will be also randomly allocated to one of three intervention arms of MET, FIBER, and MET + FIBER (Step 3, Fig. 3). Staff who completed Steps 2 and 3 will be different and will be blinded to the other step. Stratification will be based on four sex/age categories of male 12–15 years old, female 12–15 years old, male 16–18 years old, and female 16–18 years old.

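### The age and sex subgroup analysis is planned inside each arm, a non-randomised contrast that cannot separate natural course from a treatment effect that differs by subgroup

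*Protocol article*

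**What the plan says.** The section on additional analyses {20b} consists of one sentence: "We plan to do a subgroup analysis for age and sex differences within each arm". It names the two factors and places the comparison inside the arm.

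Nothing elsewhere in the article turns this into a comparison between arms:

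- Statistical methods {20a} describes the models as follows: "Intervention types and times will be included as fixed effects in linear mixed models". Covariate adjustment is mentioned there, but no term lets the intervention effect vary with age or sex.
- Sequence generation {16a} uses the same two factors for randomisation: "Stratification will be based on four sex/age categories". These are sex crossed with 12–15 and 16–18 years. The stratification is sound; it matters here because the subgroups are already defined and balanced across arms.
- Objectives {7} sets a primary objective that compares the three interventions with one another on HOMA-IR.
- Choice of comparators {6b} states: "A control group without treatment is not included".

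**The concern.** Randomisation makes arms comparable. It does not make boys comparable with girls, or 12-year-olds with 17-year-olds. A subgroup difference seen inside one arm is the sum of two things: how the subgroups would have differed anyway over 12 months, and how differently they respond to that arm's treatment. One arm cannot separate them, and no untreated arm shows the natural course. The article itself treats pubertal stage as a potential confounder for HOMA-IR, and at ages 12–18 pubertal stage is tied to age and sex.

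Running the comparison separately in three arms adds a second difficulty. The likely result is significance in some arms and not in others, which is easily read as one treatment working better in one sex or age group. The quantity that would answer that question, the difference between arms in the subgroup difference, is not planned.

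**Working it through.** The article attaches no figure to the subgroup plan, so there is nothing to reproduce. The check sets out what the planned contrast estimates and then sizes the risk of misreading.

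**What is estimated.** For arm *a*, let the mean outcome be μ(a,1) and μ(a,2) in the two subgroups.

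- Within-arm contrast: D(a) = μ(a,2) − μ(a,1) = prognostic difference + modification in arm *a*.
- Effect modification between arms *a* and *b*: D(a) − D(b). The common prognostic difference cancels.

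The plan tests D(a). A question about differential effect needs D(a) − D(b).

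**Inputs.** 30 per arm and three arms (Trial design {8}); 15% attrition (Sample size {14}). Completers per arm: 30 × 0.85 = 25.5. Per subgroup with an equal split: 25.5 / 2 = 12.75, taken as 13. The equal split is an assumption, since the article gives no expected sex or age distribution. The prognostic differences are also assumptions. They are in SD units of whatever 12-month outcome is analysed; if that is change in HOMA-IR, they are differences in change.

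**Within-arm tests with no effect modification.** With two-sided t-tests at 5%, 13 against 13, let p be the chance of significance in one arm. The chance in at least one of three independent arms is 1 − (1 − p)³.

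| Prognostic difference (SD) | p, one arm | At least one arm, formula | At least one arm, simulated |
|---|---|---|---|
| 0 | 0.050 | 1 − 0.950³ = 14% | 14% |
| 0.3 | 0.114 | 1 − 0.886³ = 30% | 31% |
| 0.5 | 0.232 | 1 − 0.768³ = 55% | 54% |
| 0.8 | 0.499 | 1 − 0.501³ = 87% | 87% |

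The simulated column is from 4,000 runs. A separate simulation of 40,000 trials gave 14% at 0 and 55% at 0.5 SD. In that run at 0.5 SD, 54% of trials were significant in some arms but not all.

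**Sensitivity to the split.** With 8 against 18 per arm instead of 13 against 13, the same formula gives 28%, 50% and 82% at 0.3, 0.5 and 0.8 SD. The message does not depend on an equal split.

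**The opposite failure.** With a real modification of 0.75 SD in the combination arm and an equal and opposite prognostic difference, D in that arm is 0.75 − 0.75 = 0. Its within-arm test then rejects in only 5% of simulated trials.

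**The interaction test.** In the 40,000-trial simulation the 2-df test of equal D across arms rejected in 4.9% to 5.0% of trials with no modification, at prognostic differences of 0, 0.5 and 0.75 SD. For one pairwise contrast, SE = √(4/13) = 0.555 SD.

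- Power at 0.75 SD: Φ(0.75/0.555 − 1.96) = Φ(−0.61) = 27%. The simulated 2-df test gave about 26%.
- Detectable with 80% power: (1.96 + 0.84) × 0.555 = 1.55 SD.
- Needed for 80% power at 0.75 SD: 2 × 4 × ((1.96 + 0.84)/0.75)² ≈ 112 analysed per arm.

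**The case against.** The strongest reply is that the sentence never claims to test whether treatment works differently by age or sex. No objective, outcome or prediction asks that question, and a purely descriptive report of age and sex differences in each arm would fit the wording. This is also one line on additional analyses in a condensed article, where model form is commonly left to a fuller document. The authors may have meant treatment effects by subgroup and written it loosely.

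Part of this stands. It bounds the point to an additional analysis and rules out three stronger readings that a reader might infer:

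- *That the within-arm contrast measures prognosis alone.* It does not; it mixes prognosis with any modification.
- *That the trial will announce responders by sex or age.* The article does plan a responder analysis, but in connection with the microbiome, and it predicts nothing by sex or age.
- *That 54% is a false-positive rate.* With a 0.5 SD difference assumed in every arm, a significant within-arm test detects something true. It becomes an error only when read as differential effect.

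The remainder does not rescue the sentence. The objection to missing detail does not apply, because the article names the comparison and places it inside the arm. If a between-arm analysis was intended, the wording says something else. If only description was intended, the text should say so, because patchy significance across arms invites the wrong inference. Low interaction power is a reason to report the right contrast cautiously, not to test a different one.

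**Conclusion.** The point holds, with limited reach. As written, the subgroup analysis yields non-randomised contrasts that cannot separate the natural course of HOMA-IR from effect modification, and differing significance across arms does not show a differential treatment effect. Under the stated assumptions (about 13 completers per subgroup per arm, no modification, a common prognostic difference of 0 to 0.8 SD), at least one arm is significant in about 14% to 87% of trials. The 14% is ordinary multiplicity from three 5% tests; the excess above it reflects a true prognostic difference open to misreading. No figure in the article fixes where in that range this trial would fall. Nothing here touches the primary between-arm comparison or the sample size, and it would be wrong to infer that it does.

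**What to change.** Replace the sentence in section {20b} with text such as:

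> Effect modification by sex and by age category (12–15 and 16–18 years, as used for stratification) will be assessed with intervention-by-subgroup-by-time terms and their lower-order terms in the linear mixed model, tested at 12 months (2 degrees of freedom per subgroup factor). Between-arm differences with 95% confidence intervals will be reported within each subgroup and labelled exploratory. Any within-arm summaries will be descriptive only.

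The cost is small but more than one model term. If the model has three arms and the two follow-up times as outcomes, each binary subgroup factor adds 1 (main effect) + 2 (by arm) + 1 (by time) + 2 (by arm and time) = 6 parameters. If baseline is also modelled as an outcome, it adds 1 + 2 + 2 + 4 = 9. Fitting one subgroup factor at a time keeps this manageable. No new data, visits or participants are needed. The main drawback is low power, about 27% for a 0.75 SD interaction under the same assumption, so a non-significant interaction must not be reported as evidence of a uniform effect.
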